### Participant timeline {13}

The complete participant timeline is illustrated in Table 1.

**Table 1 Tab1:**
[figure not shown]
SPIRIT schematic schedule of enrolment, interventions, and assessments for the NeuroNation MED trial

*Only applied in the IG.S-NAB: Screening Module of the Neuropsychological Assessment Battery; HADS-D: Hospital Anxiety and Depression Scale (German Version); HEALTH-49: Hamburg Modules for the Assessment of Psychosocial Health in Clinical Practice; CFQ-D, Cognitive Failures Questionnaire; HLQ-G: Health Literacy Questionnaire (German Version); SUS: System Usability Scale; Usage Data, completed exercises, duration of use, number of training days etc.; Diary: patient diary with activities that could have an effect on cognitive status. Exclusively at the test center of JUH, further secondary outcome measures include visual attentional parameters based on TVA; BFI: Brief Fatigue Inventory; FAS: Fatigue Assessment Scale; PHQ: Patient Health Questionnaire 9; BDI II: Beck Depression Inventory II; PTSS-14: Post-Traumatic Stress Syndrome 14-Questions Inventory; ESS: Epworth Sleepiness Scale; FACT-Cog: Functional Assessment of Cancer Therapy—Cognitive Function; TAP (Attentional Performance): computerized Test of Attentional Performance

### Sample size {14}

The assumed effect size is based on results of previous studies using the cognitive training program “NeuroNation BT” [69] and comparable digital cognitive training applications [25, 26, 36, 70]. A calculation by means of a *t*-test for independent samples was used as the basis for the sample size calculation within the trial described here. With an allocation ratio of 2:1, if 164 subjects are included in the IG and 82 subjects are included in the control group, differences with an effect size of 0.39 or greater can be shown (a priori power analysis, Wilcoxon-Mann–Whitney test (two groups), power = 80%, two tails significance level *α* = 0.05). This resulted in the total sample size of 246. We expect a drop-out rate of approximately 15% [71], which results in a sample size to be recruited of *N* = 286. This sample size calculation was performed with G*Power 3.1.

### Recruitment {15}

Potential participants are recruited via the volunteer database of the Geriatrics Research Group of the Charité—Universitätsmedizin Berlin, the Neuro-Post-COVID Center of the Department of Neurology of Jena University Hospital, the Department of Neurology of the University Hospital Cologne, the Clinic for Neurology with Experimental Neurology, Charité, and the Neuropsychological University Outpatient Clinic of the LMU Munich. At the Centre Hospitalier Neuro-Psychiatrique in Luxembourg, participants were recruited from the long-COVID consultation. Furthermore, (neuro-) rehabilitation clinics, psychotherapists in private practice, and various clinics of the Charité and the other participating study centers will be used as gatekeepers for recruitment and flyers will be distributed. In addition, announcements on intranet sites will be used, a newsletter will be sent to NeuroNation users, and outdoor and radio advertising will be used to draw attention to the study.

The planned study will include diagnosed patients with cognitive impairment (ICD-10-GM: F06.7). The study population will be recruited via the clinics of the study centers involved in the study and via external practices as multipliers, each of which is diagnosed as part of standard care. These clinics and practices will approach patients with diagnoses and characteristics matching the inclusion criteria for the planned survey. The multipliers receive flyers designed for the study that provide information on the inclusion and exclusion criteria applicable to this study. These also include, by way of example, the diagnosis relevant to this study. Thus, all potential study participants have a medically confirmed ICD-10-GM F06.7 diagnosis.

## Assignment of interventions: allocation

### Sequence generation {16a}

The randomization process in this study incorporated permuted block sizes (using block sizes that enable a 2:1 allocation), which were generated by the research coordinator of every study center. This approach aimed to maintain allocation concealment and achieve balanced participant allocation across the treatment groups, minimizing potential bias in the study.

### Concealment mechanism {16b}

To avoid selection bias, t_1_ (12 weeks after the baseline measurement) will be conducted by a different study staff member not involved in t_0_ (randomization and introduction to the training). Once baseline measurements are completed for a participant, a staff member will randomize the participant by a manual procedure using urn sampling without replacement and will not be allowed to conduct t_1_. The allocation is entered by the research coordinator of the study center into a password-protected Excel file, to which the study staff has no access. This procedure ensures that at t_1_, the research team is unaware of which treatment group a participant has been assigned to.

### Implementation {16c}

Randomization will be performed on the patient level with a 2:1 ratio using block randomization with varying block sizes, stratified per sex. Participants can be enrolled only by trained study personnel. For the intervention group, the manual and login voucher will be handed out after randomization. Subsequently, the study staff installs the app with the participants, registers them, and gives instructions on the frequency and duration of the training.

## Assignment of interventions: blinding

### Who will be blinded {17a}

Study participants in the IG will participate in an app-supported cCT program over a 12-week period, while the control group will receive standard medical care or no care. Consequently, participants will be aware of their group assignment. Thus, this design prevents blinding of the study participants of their group allocation. Thus, the study will be conducted in a single-blinded design. The two study appointments will be carried out by members of the study staff, who will be blinded to the group assignment of the respective participants at both visits. Participants will be instructed before the start of the second appointment not to make any reference to their group allocation. The blinding will not be undone until the end of the study appointment. After the second appointment, participants in the control group will be given access to the NeuroNation MED app.

### Procedure for unblinding if needed {17b}

Unblinding of the study personnel will only happen in case of serious adverse events; circumstances for medical intervention not permitted by the study protocol; intercurrent illness/infection; other significant protocol violations; personal request of the study participant (withdrawal of patient consent); and any other situation where, in the opinion of the principal investigator, continued study participation would not be in the best interest of the subject. If serious adverse events occur during the trial or performance evaluation, they must be reported to the sponsor.

## Data collection and management

### Plans for assessment and collection of outcomes {18a}

The t_0_ and t_1_ take place in the facilities of the study centers and the associated examination rooms. A Trial Master File (TMF) documents all essential communication and other processes.

The collected data from the questionnaires/assessments will be recorded in paper form and filed accordingly in the Investigator Site File (ISF). Additional notes are logged on paper as part of the data backup process and later digitally recorded. Logging data of the NeuroNation MED app usage will be provided to the study centers. Personal data documented on paper (e.g., consent forms, patient and participant files) must be stored in lockable cabinets. The allocation of keys must be organized and controlled within the study team. The allocation of keys must be documented. Controlled key distribution should ensure that only authorized study team members have access to the data. Keys are not to be given to non-authorized individuals. Lockers are to be kept locked at all times. When an employee leaves, the corresponding key must be returned immediately.

Access control to the premises is only possible for authorized persons, key allocation or transponder system.

The corresponding data storage takes place in a secured folder within the servers of the study centers. The folders are only accessible to the members of the research team. Further access requires the active activation by the rights holder of the folder. The access rights within the study team are regulated by the head of the study team; any change of these rights requires his approval. Electronically maintained participant identification lists must be secured by a password. All study data (paper and digital) will be deleted after the legally prescribed retention period of 10 years has expired.

### Plans to promote participant retention and complete follow-up {18b}

For participants who withdraw consent for any reason, their previously collected data will not be used for analyses. If participants drop out of the study or have missing data, data imputation will be performed. Moreover, if participants deviate from the intended intervention (usage of the application), the initially scheduled follow-up visit will still be conducted and the data will be utilized.

### Data management {19}

The procedure for data entry, collection, and storage is described in detail below.

Technical organizational measures:Pseudonymization of data in password-protected Case Report Form (CRF; in an Excel file).Access control to the premises (concerns offices for storage of paper documents) is only possible for authorized persons and is regulated by key allocation.In addition to the use of the app, the therapy also includes psychoeducational materials, which are sent to the participants by mail from the manufacturer’s side. In order to protect the personal data of the users and in particular to prevent the contact email addresses from being passed on outside the study centers, the centers create mail distribution lists in which the addresses of the test persons are stored. The app manufacturer has no access to this and only sends the materials to the general distribution list and has no insight into the mail addresses behind it.

Access to study-specific electronic files: PC workstations of the respective centers, server infrastructure, authorization system, password-protected access to the personal account.Data transfer within the study centers in pseudonymized form and externally in anonymized form.Regular automatic backup of study data is performed routinely.Description of the documentation procedure.

The collected data from the introductory questionnaires are recorded in paper form and filed accordingly in the ISF. Additional notes are logged on paper as part of the data backup process and later digitally transcribed.

The corresponding data storage is done in a secured folder within the network of the respective study centers. These folders are only accessible to the study staff of the respective center. Further access options require active activation by the rights holder of the folders. The access rights within the study team are regulated by the study manager; any change of these rights requires his approval.

In addition, study data is deleted after the legally prescribed retention period of 10 years has expired. Subject-related data will be collected in pseudonymized form. All subjects are unmistakably identified by a participant number, assigned upon registration. The study directors of each study center maintain a confidential participant list, in which the identification data are linked to the full subject name, to which only he and one other member of the study staff have access. Questionnaires will be stored in a lockable cabinet at the study center.

Paper records:Storage location patient file, study file, CRF: premises of the respective study centers.Restricted access room, lockable cabinets.It is not possible to trace CRF data to individual patients without an identification list.Only the study directors of each study center have access to the identification list of their participants.

### Confidentiality {27}

The questionnaires and assessments will be recorded in paper format and stored in the Investigator Site File (ISF). Additional notes will be documented on paper and transcribed digitally at a later stage. The data will be saved on secure folders within the network of each study center. These digital folders will only be accessible to the study personnel of the respective center. Any additional access requires active authorization from the folder’s rights holder. Further, the access permissions within the study team are regulated by the principal investigator, and any changes to these permissions require their approval. Furthermore, the study data will be deleted after the legally mandated retention period of 10 years. Participant-related data will be collected in a pseudonymized form where every participant will be uniquely identified by a two-digit number during registration. The study directors maintain a confidential participant list, which associates the identification data with the full participant name. This participant list is only available to the study directors and one other member of the study personnel. The paper-based questionnaires and other collected data will be kept in a lockable cabinet at the respective study center.

### Plans for collection, laboratory evaluation, and storage of biological specimens for genetic or molecular analysis in this trial/future use {33}

This is not applicable as no biological specimens or genetic material has been collected in the present study.

## Statistical methods

### Statistical methods for primary and secondary outcomes {20a}

The statistical analysis will be conducted after the last t_2_ of the last patient. Collected data from assessments, questionnaires, and usage logs will be processed and cleaned in Excel. Subsequently, the data will be analyzed using statistical programs such as SPSS, R-Studio, STATA, and Python 3.9 with statistical libraries including dplyr, ggplot2, car, NumPy, Pandas, Pingouin, and Matplotlib. Both metric and non-metric variables will be considered in the statistical analysis.

The data from the IG and CG will be initially analyzed descriptively using sociodemographic data to describe the sample, assessing the baseline status of the participants and evaluating the assessment after 12 weeks. The following descriptive statistics will be reported depending on the measurement level of each variable: frequencies (absolute and/or percentage), available and missing data counts, mean, standard deviation, standard error, lower and upper quartiles, minimum and maximum values as well as confidence intervals. Graphical representations of key variables will be generated using scatter plots, histograms, box plots, mean value plots, or other common graphics, based on the measurement level of the variables. Missing data will be included in these analyses. Therefore, datasets classified as missing not at random (MNAR) will be imputed using sensitivity analyses and a pattern mixture model, and considered further in subsequent statistical analyses.

To achieve comparability between the experimental groups at baseline, the IG and CG will be compared in terms of sociodemographic characteristics. The independent samples Welch’s *t*-test will be used for normally distributed metric variables, while the chi-square test will be employed for categorical variables. If a normal distribution is not found in the data collected, the Wilcoxon signed-rank test or Mann–Whitney *U* test will be applied. ANCOVA will be conducted to evaluate the training effects between the IG and CG, using the baseline values as a covariate and incorporating gender, experimental group (IG and CG) as independent variables, and the post-assessment score as dependent variable. Additionally, age and study center will also be examined as covariates. If the data fail to meet the assumptions for performing parametric ANCOVA, non-parametric tests such as the Wilcoxon test or Mann–Whitney *U* test will be applied instead. Effect sizes and confidence intervals will be calculated for the respective statistical tests to enhance result interpretability.

Using the logging data from the NeuroNation MED app, Pearson correlations will be used to examine the relationships between the number of training days, completed training units, and changes in assessments within the IG. Furthermore, one-way ANOVA will be employed to investigate potential associations between usage frequencies and sociodemographic data.

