## Trial design {8}

This study is a single-blinded multicenter superiority randomized controlled trial. The trial design for this study is a parallel group design with an allocation ratio of 2 to 1, indicating that two participants will be assigned to the intervention group for every one participant assigned to the control group. The framework for this trial is superiority, aiming to demonstrate the effectiveness of the NeuroNation MED training program in improving cognitive abilities compared to the wait list control group. The treatment context of the participants in both groups will not be influenced by the study. Participants can continue to receive standard care with all standard therapies they would normally receive outside of the study, or receive no therapy. The therapies administered will be documented using a participant diary.

All data will be collected and analyzed in a standardized manner, adhering to good clinical practice. This protocol is conducted according to the “Standard Protocol Items: Recommendations for Interventional Trials” (SPIRIT) checklist for clinical trials [42].

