### Criteria for discontinuing or modifying allocated interventions {11b}

Each participant of the study will be informed that participation is voluntary and that withdrawal from the study is possible at any time. It will be communicated that withdrawal will have no effect on possible further treatment at any participating institution. The study may be terminated before its intended completion if ethical concerns arise, if there is insufficient recruitment of participants, or if the safety of the participants is compromised or uncertain. Furthermore, termination may occur if changes in accepted clinical practices render it unwise to continue the clinical trial, or if early indications of harm from the intervention are observed.

Since the study follows an intention-to-treat approach, participants in the IG will not be prescribed a fixed amount of training time or session count for using the NeuroNation MED app. At the first appointment, the IG is instructed to adhere to a certain weekly usage duration and frequency of use, but this is not mandatory for study participation and may vary among participants during the intervention period.

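### With 2:1 allocation, the pooled-variance ANCOVA misstates the standard error of the primary effect if the arms differ in residual spread, and the rank-test fallback does not repair this

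*Protocol article*

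**What the plan says.** The protocol article (Statistical methods for primary and secondary outcomes {20a}) states that "ANCOVA will be conducted to evaluate the training effects between the IG and CG, using the baseline values as a covariate". The post-assessment score is the dependent variable, and group and gender are factors. Age and study center are also to be examined as covariates. No unequal-variance or heteroscedasticity-consistent standard error is named for this model. If its assumptions are not met, the same section replaces it with a rank test (Wilcoxon or Mann–Whitney). For the baseline comparison of the arms, that section says Welch's t-test "will be used for normally distributed metric variables".

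Trial design {8} sets "a parallel group design with an allocation ratio of 2 to 1". Sample size {14} works with complete arms of unequal size: "if 164 subjects are included in the IG and 82 subjects are included in the control group". Interim analyses {21b} sets the final alpha for the primary outcome at 0.04695.

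The IG may choose among four session lengths (Intervention description {11a}). Of the recommended amount of training, Criteria for discontinuing or modifying allocated interventions {11b} says that "this is not mandatory for study participation and may vary among participants during the intervention period". Section {20a} also plans to correlate training days with change in the IG.

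**The concern.** The usual ANCOVA standard error uses one residual variance for both arms. With equal arms, a difference in variance cancels out of the group comparison. At 2:1 it does not, because the pooled estimate gives the larger arm twice the weight, while the true variance of the difference depends more on the smaller arm.

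Unequal spread is plausible in this trial. If people train different amounts and the effect depends on the amount, the effect varies between people and widens the IG residuals. The planned correlation of usage with change shows that the sponsor considers such a dependence possible. The primary confidence interval and p-value would then lack their stated properties, and the written remedy is a change of test rather than a corrected standard error.

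**Working it through.** **Inputs from the article.** 164 IG and 82 control ({14}); final alpha 0.04695 ({21b}), so z = 1.987; planned effect 0.39 ({14}).

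**Assumed.** The article gives no SD by arm and no baseline–follow-up correlation. I take correlations of 0.6–0.7 and a person-to-person SD of the training effect of 0.3–0.5 outcome SDs, with effects unrelated to the outcome a person would have had untrained.

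**1. The plan's own figure.** For d = 0.39, two-sided alpha 0.05, 2:1 allocation and the Wilcoxon–Mann–Whitney test (efficiency 3/π), the required size is 164 + 82 = 246, with power 0.801. The stated figure is reproduced, and the point below does not change it.

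**2. Bias of the standard error.** Let v be the IG residual variance divided by the control residual variance.

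- Model variance: [(164v + 82)/246] × (1/164 + 1/82)
- True variance: v/164 + 1/82
- With arms of 2:1, the ratio model SE / true SE reduces to √[(2v + 1)/(v + 2)]. With 1:1 it is 1 for every v.

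The true size is 2 × [1 − Φ(1.987 × ratio)].

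| v (IG/control) | model SE / true SE | true size at 0.04695 |
|---|---|---|
| 1.14 | √(3.28/3.14) = 1.022 | 4.2% |
| 1.25 | √(3.5/3.25) = 1.038 | 3.9% |
| 1.49 | √(3.98/3.49) = 1.068 | 3.4% |
| 2 | √(5/4) = 1.118 | 2.6% |
| 1/1.25 | √(2.6/2.8) = 0.964 | 5.6% |
| 1/1.5 | √(0.875) = 0.935 | 6.3% |
| 1/2 | √(2/2.5) = 0.894 | 7.6% |

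**3. Which v is plausible.** With outcome SD 1, effect SD τ and baseline correlation ρ, v = 1 + τ²/(1 − ρ²).

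- τ = 0.3, ρ = 0.6: 1 + 0.09/0.64 = 1.14
- τ = 0.5, ρ = 0.7: 1 + 0.25/0.51 = 1.49

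This range gives an SE 2–7% too large. The 12% figure needs v = 2, which means τ of roughly 0.7 (ρ = 0.7) to 1.0 (ρ = 0).

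**4. Power lost by plain ANCOVA at the planned effect.** Take d = 0.39 outcome SDs, ρ = 0.7 and control residual variance 0.51. Power is 1 − Φ[(1.987 × SE used − d)/true SE].

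| v | model SE | robust SE |
|---|---|---|
| 1.14 | 97.2% | 97.5% |
| 1.5 | 94.7% | 96.0% |
| 2 | 89.9% | 93.5% |

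At a smaller assumed effect of 0.27, where power is about 79% with equal variances, simulation gives about 68% against 72% (v = 1.5) and 57% against 65% (v = 2).

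**5. The fallback.** The article does not say how a failed assumption is detected or which score the rank test uses. I assumed a Levene test at 0.05 as the trigger, ρ = 0.7 and 4,000 simulated trials per setting.

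- The trigger fires in about 47% of trials at v = 1.5 and about 91% at v = 2.
- With Mann–Whitney on the post score and d = 0.39, power is about 86% and 73%. With HC3 it is 96% and 94%.
- At d = 0.27 the same rule gives 58% and 41%. With Mann–Whitney on change scores it gives 66% and 55%, close to plain ANCOVA and still below HC3.
- With no effect and the control group twice as variable, the post-score rule rejects in about 6.0–6.4% of trials.

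**6. HC3.** In simulation at nominal 0.04695 (6,000 trials per setting), HC3 rejected in 4.2–4.7% for IG/control SD ratios from 0.71 to 1.4. With equal variances and d = 0.27, power was 79.2% with HC3 against 79.5% with the model SE.

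**The case against.** The strongest objection is that the choice of standard error usually belongs in the statistical analysis plan, which is not shown. The article nowhere says that equal variances are assumed and contradicts nothing on this point. That stands, and it is why this is no proven error. It does not remove the point, because the article fixes both the model and its remedy, and the remedy is the weaker one.

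A second objection is that the plan already covers failed assumptions. It does, and homogeneity of variance is one of them. But step 5 shows that the switch costs power and leaves the size above the nominal level when the control group is the more variable arm. Adding a robust standard error while keeping the switch would discard ANCOVA in just the trials where the robust error matters.

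A reader might draw four stronger conclusions that the article does not support:

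- *The standard error is off by 4–12% whenever the spreads differ.* That range belongs to variance ratios of 1.25–2, and no SD by arm is given. An SD difference of 5% gives under 2%.
- *The trial risks excess false positives.* The mechanism at hand, self-chosen training, widens the larger arm and makes the test too strict. Inflation needs a more variable control group, for which the article offers no specific reason.
- *The trial is underpowered because of this.* At 0.39 and a correlation of 0.7, plain ANCOVA stays above 80% even at v = 2.
- *Using Welch's test at baseline contradicts the ANCOVA.* These are different analyses of different variables. The contrast is worth noticing but is no inconsistency.

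**Conclusion.** The point holds in conditional form. If the IG residual variance is 1.14–1.49 times that of the control group, the model standard error is about 2–7% too large; at a ratio of 2 it is 12% too large. The test is then conservative, with true size 4.2–3.4% (2.6% at a ratio of 2). At the planned effect the power loss against a robust error is 0.3–1.3 points for ratios of 1.14–1.5 and 3.6 points at a ratio of 2. In the reverse direction, size would be 5.6–7.6% for ratios of 1.25–2.

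The larger cost lies in the fallback: about 10 points of power at a ratio of 1.5 (86% against 96%) and about 21 at a ratio of 2 (73% against 94%), if the rank test is applied to the post score. On change scores the loss is smaller. All of this rests on assumed variance ratios, a baseline correlation of 0.7 and an assumed trigger. Priority is moderate to low.

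**What to change.** Keep the baseline-adjusted ANCOVA as the primary analysis. Take the standard error, confidence interval and p-value of the group effect from a heteroscedasticity-consistent estimator (HC3) in each imputed dataset, and pool with Rubin's rules. State that unequal variance does not trigger the switch to a rank test. Apply the same to the secondary ANCOVAs.

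The cost is one or two sentences and a standard software option. If the variances are in fact equal, the interval is about 1% wider. The planned sample size does not change.

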### Methods in analysis to handle protocol non-adherence and any statistical methods to handle missing data {20c}

Excluding participants with missing values from the analysis can bias the statistical analysis. Hence, a multiple imputation approach is conducted. Missing value information will be gathered through follow-up telephone interviews when a participant withdraws from the study. These interviews will assess the reasons for discontinuation.

Within this study, all of the missing data will be imputed. This process will involve the generation and pooling of multiple complete datasets, where missing values are estimated based on the observed data. To assess the robustness of our imputations and the potential impact of missing data on the study’s primary outcome, sensitivity analysis will be conducted using delta adjustment. Moreover, an intention-to-treat analysis will ensure that every participant who took part in the baseline assessment is included in the final analysis. This includes the IG, regardless of their adherence to the proposed training protocol.

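### The primary ANCOVA gives way to a covariate-free rank test on an unstated criterion, and the place of centre in the model is left open; the cost is precision and a changed estimand, not planned power

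*Protocol article*

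**What the plan says.** All of the following is in the protocol article.

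- Section {20a} defines the training-effect analysis as an ANCOVA with the post-assessment score as outcome, "using the baseline values as a covariate and incorporating gender, experimental group (IG and CG) as independent variables".
- On the remaining covariates it says: "Additionally, age and study center will also be examined as covariates".
- It then provides for a replacement: "If the data fail to meet the assumptions for performing parametric ANCOVA, non-parametric tests such as the Wilcoxon test" or the Mann–Whitney U test are used in place of the ANCOVA. Nothing limits this to secondary outcomes. No assumption, diagnostic or threshold is named, the choice between the tests is open, and it is not stated whether the test is run on post scores or change scores.
- For the comparison of the arms at baseline, the same section says: "If a normal distribution is not found in the data collected, the Wilcoxon signed-rank test" or the Mann–Whitney U test.
- Section {16a} says that the permuted blocks were "generated by the research coordinator of every study center". Section {16c} describes "block randomization with varying block sizes, stratified per sex".
- Section {20c} plans multiple imputation with "generation and pooling of multiple complete datasets".
- Section {14} sizes the trial at 164 and 82 participants for an effect size of 0.39, naming the Wilcoxon-Mann–Whitney test with 80% power at two-sided alpha 0.05. Section {21b} reserves alpha 0.04695 for the final primary analysis.

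**The concern.** The confirmatory analysis is not one analysis but a choice made after looking at the data, on a criterion that the reader cannot reconstruct. Three things follow.

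1. **Adjustment.** Neither named test accepts covariates. If it is run on post scores, baseline S-NAB, sex, age and centre all leave the primary comparison.
2. **Estimand.** ANCOVA estimates an adjusted mean difference in the S-NAB index. A rank test addresses whether scores in one arm tend to exceed those in the other. The subgroup results in section {20b}, which are reported as η², would then be on a different scale from the primary result. The interim look at 50 participants and the final analysis could also end up using different tests.
3. **Centre.** Because each centre produces its own lists, centre is in effect a randomisation factor. It is also plausibly prognostic: section {15} shows that some centres recruit from post-COVID or long-COVID services and others do not. Yet its place in the model is not settled.

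At stake are the precision of the primary estimate and the certainty that the reported analysis is the only one that could have been reported.

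**Working it through.** **Inputs.** From section {14}: 164 and 82 participants, d = 0.39, two-sided alpha 0.05, power 80%. From section {21b}: final alpha 0.04695. The documents give no baseline–post correlation r, so it is assumed over a range.

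**Step 1: reproduce the stated sample size.** Power comes from a noncentral t with noncentrality d × √(n1·n2/(n1+n2)). For the Wilcoxon-Mann–Whitney test, both sample sizes are multiplied by the normal-theory efficiency 3/π = 0.955.

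- 164 × 82 / 246 = 54.67, and 54.67 × 0.955 = 52.20.
- Noncentrality = 0.39 × √52.20 = 2.82, which gives power 80.1% at alpha 0.05.
- The smallest 2:1 design that reaches 80% is 164 + 82 = 246, the protocol's figure. A plain t-test would need 237.

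So 246 is the sample size for an unadjusted rank test. At alpha 0.04695 the same test has 79.4%.

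**Step 2: the adjusted model.** Adjusting for baseline multiplies the residual variance by 1 − r², so the effective effect size is 0.39/√(1 − r²). For r = 0.5 this is 0.39/0.866 = 0.450, with noncentrality 0.450 × √54.67 = 3.33. The last column is the factor by which an unadjusted rank test would need more patients to match ANCOVA, 1/[(1 − r²) × 3/π]. Power is at alpha 0.04695.

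| Assumed r | ANCOVA power | Mann–Whitney on post scores | Sample-size factor |
|---|---|---|---|
| 0.3 | 84.7% | 79.4% | 1.15 |
| 0.5 | 90.8% | 79.4% | 1.40 |
| 0.7 | 97.9% | 79.4% | 2.05 |

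In terms of precision, the ANCOVA standard error is √(1 − r²) times that of an unadjusted mean difference: 0.95, 0.87 and 0.71.

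**Step 3: a rank test on change scores.** The wording would also allow this. If 0.39 is in post-score SD units, the effect becomes 0.39/√(2(1 − r)), and power at alpha 0.05 is 66%, 80% and 95% for r = 0.3, 0.5 and 0.7. ANCOVA at alpha 0.05 has 85%, 91% and 98%.

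**Step 4: how a switch behaves.** A simulation used 8,000 trials per setting, 164 against 82, r = 0.5 and 0.7, alpha 0.05, and residuals that were normal, t with 5 degrees of freedom, or mildly skewed. The switch was triggered by Shapiro–Wilk p < 0.05 on the residuals. That trigger is an assumption; the protocol names none.

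- The switch occurred in about 5% of normal datasets and in 87–98% of the non-normal ones. In the non-normal ones ANCOVA still held its type I error (4.7–5.2%).
- Power under the non-normal settings fell from about 91% to 86% (t) and 82% (skewed) at r = 0.5, and from about 98% to 85% and 81% at r = 0.7.
- Type I error of the mechanical rule was 4.8–5.4%.
- Type I error when the smaller of the two p-values was taken was 6.9–9.0%.

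**The case against.** The strongest reply is that the fallback is the very test for which the trial was sized. That stands. A reader might infer from the power gap that a switch leaves the trial underpowered. The documents do not support this: the rank test on post scores has 80.1% at alpha 0.05, and even under the simulated non-normality the two-stage rule stayed at 81–86%. What is lost lies above plan, and at a correlation of 0.3 it is only about 5 percentage points.

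Other stronger readings also fail.

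- **Alpha is not controlled.** A rule applied mechanically keeps type I error near 5%. The 7–9% needs an analyst who picks the more favourable test, and nothing in the text provides for that. What remains is that an unstated criterion leaves room for choice.
- **A formal normality test decides.** None is named. How assumptions are checked may be set out in an analysis plan that is not shown.
- **Covariates are selected on the result.** The wording on age and centre can also mean that they are simply added. It is ambiguous and does not describe selection. Sex, the only factor that section {16c} names, is already in the model.
- **The primary test could be a paired test.** The signed-rank test is named only for the baseline comparison. It is a slip there, because a paired test cannot compare independent arms.
- **A rank result could not be pooled over imputations.** A rank-based location shift with a standard error can be pooled.

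It is also inferred, not stated, that baseline is dropped. A rank test on change scores would use it in part. What the reply does not remove is that the text makes the rank test a substitute and not a sensitivity analysis, gives no criterion, and names only tests without covariates. An analysis plan that followed this text would inherit the switch.

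**Conclusion.** The point holds as one of precision, estimand and pre-specification. Section {20a} allows the baseline-adjusted primary analysis to be exchanged for a covariate-free test on grounds that it does not state, and leaves the role of centre undecided although lists are made by centre. For an unadjusted rank test on post scores, the cost at alpha 0.04695 is a fall from about 85%, 91% or 98% power to about 79%, for assumed correlations of 0.3, 0.5 and 0.7. These figures rest on those assumed correlations, on the effect of 0.39 being in post-score SD units, and on normal-theory efficiency for the rank test. Planned power is not lost, and a mechanical switch does not materially inflate type I error. This should be corrected before unblinded analysis, but it does not invalidate the design.

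**What to change.** State one primary analysis: ANCOVA of the t1 S-NAB index on group, baseline S-NAB, sex and centre, with age added if wanted. Fix the covariate set in advance and remove the assumption-triggered switch. Deal with unequal variances or non-normal residuals through heteroscedasticity-robust or bootstrap standard errors. Keep a baseline-adjusted rank analysis as a sensitivity analysis only. Use the same model at the interim and final looks. Delete the signed-rank test from the between-group baseline comparison.

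The cost is a change of wording and about five degrees of freedom for six centres. With 246 participants, a model with intercept, group, baseline, sex and five centre terms leaves 246 − 9 = 237 residual degrees of freedom. No new data are needed.
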